#### Self-reported depression severity

The PHQ-9 is a brief, patient-reported depression severity measure [36]. The PHQ-9 is unidimensional [38], has good test–retest reliability [39], and has validated thresholds of mild, moderate, moderately severe and severe depression [36]. The PHQ-9 accurately discriminates differential treatment response among groups independently judged to have persistent MDD, partial remission, and full remission [39]. The PHQ-9 has a valid threshold for determining depression remission (less than 5) [39], and an established threshold for minimal clinically significant difference for individual change (5 points on 0–27 point scale) [39].

#### Interviewer-rated depression severity

The 6-item Maier subscale [40] of the HDRS-17 [37] is a semi-structured, interviewer-rated measure that is administered by treatment-blinded assessors. The Maier subscale was developed using Rasch analyses and provides a unidimensional subscale that has equivalent or greater sensitivity to treatment effects compared with the HDRS-17 [41, 42]. The Maier subscale has been recommended specifically for depression treatment trials in patients with medical comorbidities because the measure includes no somatic items [42]. The Maier has a valid cutoff for remission (4 or less) [42].

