#### Power analysis and sample size

The power analysis was conducted in G*Power, Version 3.1 using F test for Test family and ANOVA: Repeated measures, within-between interaction for Statistical test. We estimated the sample necessary for detecting a Condition (2 levels of between-subjects factor: Intervention vs. Control) × Time (2 levels of within-subjects factor: 0 and 4 months) interaction on the primary outcomes of depression severity (i.e., 9-item Patient Health Questionnaire (PHQ-9; [36]) and Hamilton Depression Rating Scale (HDRS-17; [37]). We did not include 3 time-points as this assumes linear change across all 3 time points in G*Power 3.1, and we expected change between 0 and 4 months for the intervention condition, followed by stability between 4 and 8 months. The effect size (Cohen’s *f* = 0.18) was from our previous meta-analyses [15] regarding the effect of exercise training on depressive symptoms in persons with MS. The power analysis included assumptions of reliability for the within-subjects factor of ICC = 0.50, two-tailed *α* = 0.025, and *β* = 0.05 (i.e., 95% power); the *α* = 0.025 was selected based on two primary outcomes. The power analysis indicated the minimal total sample size for testing the Time × Condition interaction of 122 participants (61 per group), and we anticipate a dropout rate of ~ 20% resulting in a projected recruitment of 146 participants.

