### Outcomes

#### Overview

The primary outcomes are the PHQ-9 [36] and HDRS-17 [37] as measures of depression symptom severity appropriate for MDD, whereas the secondary outcomes include measures of fatigue, cognitive performance, and HRQOL. The tertiary outcomes are exercise behavior, accelerometry as a device-based measure of free-living PA, and aerobic and muscle fitness. All outcomes will be assessed at baseline (0 months), immediate follow-up (4 months), and long-term follow-up (8 months) by treatment-blinded assessors. The assessors will not be involved in random assignment or delivery of the conditions, and will not directly communicate with the behavior coaches about participants. Participants themselves will be instructed not to discuss exercise routines with assessors, and why it might bias the evaluators.

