#### Primary outcome measures

We include two outcomes for depression severity, as one is self-reported (primary) and the other is a semi-structured, interviewer-rated measure (secondary). The logic is that the self-report change in depression severity should be confirmed with the semi-structured, interviewer-rated change, as change in the former is more likely, but could represent a self-report bias associated with participants not being blinded regarding treatment condition.

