### Data analyses

#### Overview

The data analyses will be overseen by a biostatistician and follow intent-to-treat (ITT) principles (i.e., include all persons regardless of dropout). We will perform exploratory data analyses only among those who complete immediate and long-term follow-up testing (i.e., completer’s or per protocol analysis). We will check the data for errors and outliers, and lock the data set before analyses. The analytic plan will account for potential confounders of the intervention effect on the outcomes. The confounders may include MS duration, BMI, age, sex, disease-modifying therapy, and relapse rate. We will include any of those variables and others that differ between conditions as covariates in the following analyses.

#### Data analysis – aim 1

The first analysis tests the hypothesis that those who are randomly assigned into the intervention condition (i.e., exercise training) will demonstrate (a) reductions from baseline in depression severity that (b) are sustained over 4-months of follow-up compared with those in the control condition (i.e., stretching). The hypothesis will be tested using a linear mixed model in JMP Pro 16.0. The linear mixed model will include condition and time as fixed effects, and subject nested within condition as a random effect using unbounded variance components and the REML method (https://www.jmp.com/content/dam/jmp/documents/en/academic/learning-library/08-repeated-measures-analysis-(mixed-model).pdf). The hypothesized interaction term will be decomposed with follow-up tests, and differences in comparison of mean scores will be expressed as Cohen’s d with standard guidelines for interpretation. The final models for PHQ-9 and HDRS-17 scores will be adjusted for covariates. The overall Type I error will be controlled based on an adjustment of alpha (two-tailed *α* = 0.025) given the two primary outcomes in Aim 1.

#### Data analysis – aim 2

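### The interviewer-rated primary outcome is the HDRS-17 in the power, outcome and analysis text but the 6-item Maier subscale in its own definition, and its primary status is also contradicted

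*Protocol article*

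**What the plan says.** **HDRS-17 as primary.** The Power analysis and sample size section plans for a condition-by-time "interaction on the primary outcomes of depression severity (i.e., 9-item Patient Health Questionnaire (PHQ-9; [36]) and Hamilton Depression Rating Scale (HDRS-17; [37"]). The Outcomes overview says "The primary outcomes are the PHQ-9 [36] and HDRS-17 [37] as measures of depression symptom severity appropriate for MDD". Data analysis – aim 1 says "The final models for PHQ-9 and HDRS-17 scores will be adjusted for covariates" and splits alpha because there are two primary outcomes. The Methods part of the abstract names the Hamilton scale without saying how it is scored.

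**Maier subscale as the definition.** The section Interviewer-rated depression severity is the only place where this measure is described. It says "The 6-item Maier subscale [40] of the HDRS-17 [37] is a semi-structured, interviewer-rated measure that is administered by treatment-blinded assessors". It then sets the subscale against its parent scale, saying that it "provides a unidimensional subscale that has equivalent or greater sensitivity to treatment effects compared with the HDRS-17", adds that it contains no somatic items, and gives a threshold for that score only: "The Maier has a valid cutoff for remission (4 or less"). The Maier subscale is not mentioned in any other section.

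**Status.** The section Primary outcome measures says that "one is self-reported (primary) and the other is a semi-structured, interviewer-rated measure (secondary"). The interviewer rating is there to confirm the self-report, which could be biased because participants are not blinded.

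**The concern.** A primary test needs one variable. Here an analyst who follows the Aim 1 text would model a 17-item total, and one who follows the outcome definition would model six items. Both would be following the protocol.

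The choice matters more than usual because of the role given to this measure. It is the blinded check on a PHQ-9 change that might be reporting bias. The protocol's reason for the Maier subscale, in patients with a medical comorbidity, is the absence of somatic items. The sample has MS, and the secondary-outcomes text expects fatigue to move together with depression. Which items enter the score could therefore affect what a confirming result means.

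The alpha split holds the overall error at 0.05 only if each of the two tests is a single pre-specified variable. The secondary label adds a second ambiguity: whether this test belongs in the split at all.

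**Working it through.** **1. The passages side by side**

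| Section | Score named | Status |
|---|---|---|
| Abstract, Methods | Hamilton scale, scoring not stated | primary |
| Power analysis and sample size | HDRS-17 | primary, alpha 0.025 |
| Outcomes, Overview | HDRS-17 | primary |
| Primary outcome measures | interviewer-rated measure, not named | labelled secondary |
| Interviewer-rated depression severity | 6-item Maier subscale | placed with the primary measures |
| Data analysis – aim 1 | HDRS-17 | primary, alpha 0.025 |

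The score and the status each take two values, and no sentence reconciles either.

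**2. The plan's own sample size**

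Inputs from Power analysis and sample size: f = 0.18, ICC = 0.50, "two-tailed *α* = 0.025, and *β* = 0.05 (i.e., 95% power"), k = 2 groups, m = 2 times.

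Formula for the within-between interaction: λ = f²·N·m/(1 − ICC), with df1 = (k − 1)(m − 1) = 1 and df2 = (N − 2)(m − 1).

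- N = 120: λ = 0.0324 × 120 × 2/0.5 = 15.55, power 0.952. This is the smallest even N that reaches 0.95.
- N = 122 (stated): λ = 15.81, power 0.955.

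The stated 122 is reproduced to within two participants. Only a standardized effect and an ICC enter the formula, so the result is the same whichever score is named. The two scores might in truth have different ICCs, which the document does not give. Over an assumed range, the required N would be 144 (ICC 0.4), 120 (0.5) and 96 (0.6).

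**3. Error rate with one fixed score**

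Two tests at 0.025 sum to 0.05. If independent: 1 − 0.975² = 0.0494. This is what the plan intends.

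**4. Error rate if either interviewer-rated score may serve**

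This step rests on two assumptions that the document does not supply: all 17 items are rated, and the two test statistics are bivariate normal with correlation r. The two-sided 0.025 critical value is 2.241. The quantity is P(|Z1| > 2.241 or |Z2| > 2.241) under the null.

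| Assumed r | Type I error for this endpoint | Ratio to 0.025 |
|---|---|---|
| 0.7 | 0.043 | 1.72 |
| 0.8 | 0.040 | 1.61 |
| 0.9 | 0.036 | 1.45 |

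Adding 0.025 for the PHQ-9 gives an upper bound on the error across the primary family of 0.036 + 0.025 = 0.061 to 0.043 + 0.025 = 0.068, against the intended 0.05.

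**5. If only the six Maier items are rated**

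No 17-item total exists, so there is no choice between scores and no inflation. The HDRS-17 model in the Aim 1 text then cannot be fitted as written.

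**The case against.** The strongest defence is that only one score is ever defined. The other sections can be read as naming the parent instrument, with the definition section saying which score is taken from it. The rationale and cutoff there all point to the Maier subscale. This has force: it shows which way the conflict should be settled. It does not remove the conflict. The Aim 1 text refers to HDRS-17 scores as what is modelled, the definition section treats the subscale and the full scale as two measures to be compared, and nothing says that one term is shorthand for the other.

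A reader might also infer that both scores come from one interview, so that the analyst can pick the better result and the error rate is in fact inflated. The document does not support that. It never says that all 17 items are rated, and its wording is compatible with giving only the six. The figures in step 4 are what would follow from free selection under an assumed correlation. They are not a property of the written plan.

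Nor does the protocol say that the HDRS-17 total is unsuitable in MS. It reports a recommendation for the Maier subscale and the reason for it.

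Finally, this is not detail that an article may leave to a statistical analysis plan. Nothing is omitted: two different scores are stated for the same test.

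**Conclusion.** The contradiction stands on the current text. The variable for one of the two tests at alpha 0.025 is not fixed, and whether that test is primary is stated both ways.

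The size depends on a fact that the document does not give. If all 17 items are rated and either score could serve, the error for this endpoint is about 0.036 to 0.043 instead of 0.025, for an assumed correlation of 0.9 to 0.7. If only six items are rated there is no inflation, but the stated analysis cannot be carried out. The text needs correction in either case.

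A reader might suspect that the sample size is also wrong because it was planned on the wrong score. It is not affected: the calculation uses no scale-specific quantity, and 122 is reproduced. Random assignment and blinded assessment are not affected either.

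**What to change.** Before any unblinded look at outcome data:

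1. Name one interviewer-rated score in the abstract, Power analysis and sample size, Outcomes overview, Interviewer-rated depression severity and Data analysis – aim 1. On the protocol's own rationale this is the 6-item Maier subscale.
2. State whether all 17 items are rated. Only if they are, list the HDRS-17 total as a supportive analysis with no share of the primary alpha.
3. Reconcile the secondary label in Primary outcome measures with the two-outcome alpha split. Either the interviewer-rated score is the second primary outcome at 0.025, or it is secondary and the alpha statements in the power and Aim 1 sections need revision.

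The first two changes cost only wording: no recalculation, and no change to data collection, provided that the score named is one that the assessors already obtain. For the third, keeping two primary outcomes leaves the sample size as it is. At the article's status date, 18 of the planned 146 participants had been enrolled.

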#### Secondary outcome measures

We will include the secondary end-points of fatigue [43], cognitive performance [44], and HRQOL [45], as changes in depression are often accompanied by changes in fatigue, neuropsychological function, and HRQOL [3]. These outcomes will anchor depression changes with other clinical end-points of substantial relevance for persons with MS who have MDD.

#### Fatigue

The perception of fatigue severity will be measured using the Fatigue Severity Scale (FSS) [43]. The FSS has 9 items rated on a 7-point scale regarding the severity of fatigue symptoms during the past 7 days. The item scores are averaged into a measure of fatigue severity that ranges between 1 and 7. FSS scores of 4 or above are indicative of severe MS-related fatigue [43], and the MDC for the FSS is 1.9 points [46]. There is evidence for the internal consistency, test–retest reliability, and validity of FSS scores as a measure of fatigue severity in MS [43].

#### Cognitive performance

Cognitive performance is a secondary outcome that will be assessed using the Brief International Cognitive Assessment for MS (BICAMS) [44]. The BICAMS battery includes the Symbol Digit Modalities Test (SDMT), first five learning trials of the California Verbal Learning Test-II (CVLT-II), and first three learning trials of the Brief Visuospatial Memory Test-Revised (BVMT-R) for measuring information processing speed, verbal learning and memory, and visuospatial learning and memory, respectively [44, 47]. The SDMT involves pairing 9 abstract geometric symbols with single digit numbers in a key, and orally stating the correct numbers for unpaired symbols as rapidly as possible for 90 s. The primary outcome of the SDMT is the number of correct responses provided in 90 s (i.e., raw score). The CVLT-II involves an examiner reading aloud a list of 16 words (four items belonging to four categories such as vegetables, animals, furniture, modes of transportation) that are randomly arranged; this is done five times in the same order at a rate of approximately one word per second. Participants recall as many items as possible, in any order, following each reading of list. The primary outcome of the CVLT-II is the total number of correct words identified over the five trials (i.e., raw score). The BVMT-R involves three trials of the examiner presenting a 2 × 3 array of abstract geometric figures approximately 15 inches in front of the participant for 10 s. The array is then removed and participants draw the array as precisely as possible with the figures in the correct location. Each drawing is scored based on accurately portraying each figure and its correct location using a 0–2 scale. The primary outcome of the BVMT-R is the total raw score across the three trials. There are benchmark scores for the cognitive tests included in the BICAMS that are associated with specific degrees of impairment in work status [48].

#### HRQOL

The 29-item Multiple Sclerosis Impact Scale (MSIS-29) [45] provides a disease-specific measure of physical (20 items) and psychological (nine items) HRQOL. The scores range between 0 and 100 with lower MSIS-29 scores representing higher HRQOL. There is evidence for the reliability and validity of the MSIS-29 in samples of persons with MS [45, 49].

#### Tertiary outcome measures

We will measure change in exercise behavior using the Godin Leisure-Time Exercise Questionnaire (GLTEQ) [50] and minutes/day of moderate-to-vigorous physical activity (MVPA) from accelerometry as a measure of free-living physical activity. We will measure aerobic capacity and muscle strength using accepted measures and protocols in MS [51]; this permits an additional check on the manipulation of performing the GEMS exercise-training protocol.

#### Self-reported exercise behavior

The GLTEQ measures the frequency of strenuous, moderate, and mild physical activity performed for periods of 15 min or more over a 7-day period [50, 52], and it will be scored as the Health Contribution Score (HCS) [28]. The HCS only includes strenuous and moderate physical activity. The HCS is computed by multiplying the frequencies of strenuous and moderate activities by 9 and 5 METs, respectively, and then summing the weighted scores. The HCS can be converted into one of three categories, namely, insufficiently active (i.e., score < 14 units), moderately active (i.e., score between 14 and 23 units), and active (i.e., score ≥ 24 units).

#### Device-measured free-living physical activity

The ActiGraph model GT3X + accelerometer (Actigraph Corporation, FL) worn during a seven-day period will provide a measure of free-living physical activity as minutes/day of MVPA. The ActiGraph accelerometer will be placed on an elastic belt that is worn snuggly around the waist over the non-dominant hip during the waking hours of a seven-day period. The data from the ActiGraph accelerometer will be downloaded and processed using the low frequency extension (i.e., filter for increasing the devices sensitivity) into one-minute epochs using ActiLife software (Actigraph Corporation, FL), and then scored for wear time and minutes/day of MVPA using MS-specific cut-points [53]. Only data from valid days (wear time ≥ 600 min) will be included in the analyses [53] and this will be confirmed with the compliance log. We will average data over two or more valid days for the outcome of minutes/day of MVPA, as this provides a reliable estimate of free-living physical activity behavior over a seven-day period [53]. Other measures such as steps/day and minutes/day spent in light physical activity and sedentary behavior [54] can be generated as additional end-points for understanding change in free-living physical activity.

#### Aerobic capacity

Cardiorespiratory fitness will be operationalized as peak oxygen consumption (VO_2peak_) and peak power output (watts or W) derived from a maximal, incremental exercise test on an electronically-braked, computer-driven cycle ergometer (Lode BV, Groningen, The Netherlands) and a calibrated open-circuit spirometry system (TrueOne, Parvo Medics, Sandy, UT) for analyzing expired gases [55, 56]. The incremental exercise test initially involves a brief, 3-min warm-up at 0 W. The initial work rate for the incremental exercise test is 0 W, and the work rate continuously increases at a rate of 15 W/min (0.25 W/sec) until participants reach maximal exertion defined as volitional fatigue. Oxygen consumption (VO_2_), respiratory exchange ratio (RER), and W are measured continuously by the open-circuit spirometry system and expressed as 20-s averages. Heart rate (HR) is displayed using a Polar HR monitor (Polar Electro Oy, Finland), and HR and rating of perceived exertion (RPE) are recorded every minute. VO_2peak_ is expressed in ml kg^−1^ min^−1^ and peak power output is expressed in W based on the highest recorded 20-s values when two or more of the following criteria are satisfied: (1) VO_2_ plateau with increasing W; (2) RER ≥ 1.10; (3) peak HR within 10 beats per minute of age-predicted maximum (i.e., ~ 1 SD); or (4) peak RPE ≥ 17 [55, 56].

#### Muscle strength

Bilateral, isometric knee extensor (KE) and knee flexor (KF) peak torque will be measured using an isokinetic dynamometer (Biodex System 3 Dynamometer, Shirley, NY) [51, 57]. Participants will be seated on the dynamometer consistent with the manufacturer's recommendations. Isometric torque will be assessed at 3 joint angles of 45°, 60° and 75°. Per joint angle, participants perform three, 5-s maximal knee extensions and one, 5-s maximal knee flexion. There is a rest period of 5-s between contractions within a set, and the rest period is 1 min between sets. The highest recorded peak torque for the stronger leg, regardless of joint angle, represents KE and KF isometric strength (N·m) [51, 57].

### Random assignment

After collection of baseline data, participants will be randomly assigned into either the exercise training condition or the control condition using a computerized process based on a random numbers sequence, and group allocation will be concealed. Participants will not be informed directly that the exercise training condition represents the experimental treatment condition and the stretching condition (i.e., attention and social contact control condition) represents the control condition, as both conditions are based on guidelines and likely have benefits in MS. To do this, the study will be advertised as comparing two different exercise approaches for managing consequences of MS and improving health indicators among persons with MS. We will measure treatment credibility after the first assigned treatment session using an adaptation of the Reaction to Treatment Questionnaire (RTQ) [58].

### Intervention condition – home-based aerobic and resistance exercise training

The proposed trial will deliver the Guidelines for Exercise in MS (GEMS) program, as fully described in our previous research [18–22], within a remotely coached/guided, home-based setting using telerehabilitation (i.e., Zoom). The schematic of the main program components is provided in Fig. 1 and the components are summarized in Table 2. The intervention condition consists of six main components: (1) three different progressive trajectories of aerobic/resistance exercise prescriptions for individualization (Orange, Blue, and Green; Table 3) that are based on current guidelines for adults with MS who have mild-to-moderate disability (i.e., defined as EDSS 0–7) [23, 24], (2) appropriate exercise equipment including a CW-300 pedometer (NEW-LIFESTYLES, INC., Lee’s Summit, MO) and set of elastic resistance bands (Black Mountain Products, McHenry, IL), (3) one-on-one coaching, (4) action-planning via calendars, (5) log books for self-monitoring, and (6) SCT-based newsletters. Of note, the current exercise guidelines specify 30 + minutes of moderate-intensity aerobic exercise 3 time per week and resistance training targeting major muscle groups 3 times per week [23, 24]. Walking is the aerobic exercise modality based on it being the most commonly reported mode of exercise among people with mild MS [59] and the intensity walking is controlled based on a step rate of 100 steps per minute as this corresponds with moderate-intensity exercise in persons with MS [60]. The resistance training stimulus consists of 1–2 sets involving 10–15 repetitions of 5–10 exercises that target the lower body, upper body, and core muscle groups. The specific lower body exercises are the chair raise, calf raise, knee flexion, knee extension, and the lunge; the specific upper body resistance exercises are the shoulder row, shoulder raise, elbow flexion, and elbow extension; and the specific core exercise is the abdominal curl. The one-on-one coaching (i.e. weeks 1, 2, 3, 4, 5, 7, 11, and 15) focuses on three main components: (1) exercise training guidance and oversight, (2) discussion of the behavioral strategies of action planning and self-monitoring, and (3) presentation and discussion of newsletters based on SCT constructs (i.e., outcome expectations, self-monitoring, goal-setting, self-efficacy, barriers, and facilitators) for optimizing adherence and compliance (Table 4) [18–22]. We further provide all participants with an NMSS educational packet “Minimizing your risk for falls: A guide for people with MS”, and a study-specific instruction sheet on fall prevention. Participants are instructed to document any falls and other concerns or adverse events in the exercise adherence log and report these during one-on-one coaching, and all adverse events will be documented and reported per UIC IRB guidelines.
